## Methods/design

### Overall study design

Women diagnosed with PCOS will be recruited at the Grace Fertility and Reproductive Medicine Centre in Vancouver, Canada. This study follows a factorial design (Fig. 1). Participants will be randomized with a 1:1 allocation into two groups: the first group participating in a comprehensive lifestyle intervention program provided by our clinic (“Graceful Lifestyle Changes” (GLC) program) while the second group will be prescribed letrozole to induce ovulation, with the standard physician counseling (Fig. 2). Within each group, participants will be further randomized with a 1:1 allocation to either receive oral myo-inositol or a placebo. Block randomization will be performed at both stages using a computer-generated random numbers table and the software program REDCap. All clinicians, research scientists and participants involved in the study will be blinded to block sizes and allocation of myo-inositol/placebo. A researcher not involved in the study will be responsible for the randomization procedures. A data monitoring committee will not be necessary given the known safety of the proposed interventions. The SPIRIT 2013 Checklist for trial protocols has been included (see Additional file 1).

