In addition to a low-glycemic diet, physical activity, and stress reduction, a diet supplemented with myo-inositol may provide further hormonal homeostasis and improve metabolic functioning [20]. Myo-inositol is one of nine stereoisomers of inositol and sometimes considered a member of the B complex vitamin family, albeit humans can synthesize this isomer from glucose. It acts as a second messenger in insulin signaling pathways. Several studies have shown that insulin resistance with its compensatory hyperinsulinemia play a pivotal role in both the metabolic and ovarian hormone dysfunction observed in PCOS women. There is evidence that women with PCOS and insulin resistance could be deficient in myo-inositol which would impact glucose metabolism. In addition, myo-inositol levels in follicular fluid are lower in PCOS women with hyperinsulinemia compared to healthy women [21, 22]. An earlier study described that higher levels of myo-inositol in follicular fluid correlated with oocyte quality and maturity [23]. When supplemented with myo-inositol, women with PCOS have experienced reduced serum insulin, testosterone, and increased rates of ovulation [24, 25]. Myo-inositol has also been shown to improve oocyte number and quality [26].

We hypothesize that implementing a comprehensive program of lifestyle changes in women with PCOS will help restore ovulation by weight loss, reduce serum androgen levels and increase sensitivity to insulin. A lifestyle change program could also ameliorate hirsutism over time. Such changes should improve overall psychological well-being and quality of life. Finally, we expect that distinct phenotypes of PCOS will respond differently to lifestyle intervention. Such information will allow us to better determine which phenotypes are best served using our comprehensive approach, and to identify more specifically those factors affecting outcomes.

The objectives of this study are: to determine whether the comprehensive lifestyle intervention described is effective in restoring ovulation and compare this to letrozole; to determine whether the addition of myo-inositol improves ovulation rates, insulin resistance, metabolic parameters; and finally to evaluate differences in the responses for each of four main PCOS phenotype sub-groups.

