## Statistical methods

The participants’ biochemical and hormonal profiles, physical attributes (body mass index (BMI), hirsutism), ovulatory response, pregnancy status, scores for depression, anxiety, stress and quality of life will be assessed for statistical normality. Each main effect will be compared by analysis of variance (ANOVA) or its non-parametric equivalents. The primary comparison will be between GLC and letrozole. The observed effects of myo-inositol alone are small in clinical experience and there are no reported interactions between myo-inositol and ovulation-induction medications or lifestyle change in the literature. Hence, our power calculations (see below) have been based on the two main effects acting independently. However, our factorial design will provide an opportunity to explore potential interactions (acknowledging the sample size required would change in the presence of interactions) [30, 31]. Categorical data will be compared by chi-square statistics. Differences in dietary intake and dietary composition over time will be compared by ANOVA or its non-parametric equivalent with time as the repetitive measure. Regression analysis will also be performed to determine the individual impacts of diet, activity, and mindfulness on ovulation. In addition, membership in the four PCOS sub-groups will be further explored as a potential predictor for ovulation rates in regression analysis after adjusting for BMI and age.

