## Trial status

This trial is yet to begin recruitment. Anticipated start date is October 2018.

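### Phenotype has its own objective but is named neither as a stratification factor nor as a covariate in the GLC-versus-letrozole comparison: a modest loss of precision and chance balance, cheap to repair before recruitment

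*Protocol article*

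**What the plan says.** All references are to the protocol article.

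- **Allocation (Overall study design).** First stage: "Participants will be randomized with a 1:1 allocation into two groups", GLC or letrozole. Second stage: "Within each group, participants will be further randomized with a 1:1 allocation to either receive oral myo-inositol or a placebo". Method: "Block randomization will be performed at both stages using a computer-generated random numbers table and the software program REDCap". Block sizes are concealed, and a researcher outside the study runs the procedure. No stratification factor is mentioned.
- **Objectives (Background).** The last of three objectives is "finally to evaluate differences in the responses for each of four main PCOS phenotype sub-groups". The hypothesis paragraph adds that "we expect that distinct phenotypes of PCOS will respond differently to lifestyle intervention".
- **Analysis (Statistical methods).** GLC against letrozole is the primary comparison. Main effects are tested by ANOVA or a non-parametric equivalent, and categorical data by chi-square. Phenotype enters only afterwards: "membership in the four PCOS sub-groups will be further explored as a potential predictor for ovulation rates in regression analysis", adjusted for BMI and age.
- **Timing (Trial status).** "This trial is yet to begin recruitment".

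**The concern.** Blocks keep the arms equal in total size. They do not keep them equal within a phenotype. Phenotype follows from the diagnostic work-up at entry, so it can be known before allocation. The Background ties the phenotypes to ovulatory dysfunction, androgen excess and ovarian morphology. The primary outcome is ovulation, so phenotype may well be prognostic, and the article itself treats it as a possible predictor.

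Two things are at stake. First, a rare phenotype may by chance fall mostly in one arm, which weakens the comparison that the third objective needs. Second, if phenotype predicts ovulation, an unadjusted chi-square test leaves that variation in the error term of the primary comparison, and any chance imbalance moves the estimate.

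**Working it through.** **Inputs.** From the article: 240 women, 120 per main arm; 70% ovulation on letrozole and 50% on lifestyle; two-group comparison of proportions at 5% significance and 80% power. Assumed, because no phenotype shares or phenotype-specific ovulation rates are given: phenotype sizes of 12 to 72 women (5-30%) and ovulation differences of 20-40 points between one phenotype and the rest.

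**1. The plan's own figure.** For the median row of Table 1, with unpooled variance and a two-sided test:

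n per group = (1.960 + 0.842)² × (0.70×0.30 + 0.50×0.50) / 0.20² = 7.849 × 0.46 / 0.04 = 90.3, so 91 per group and 182 in total.

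This matches the article. The calculation makes no allowance for phenotype.

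**2. Split of one phenotype between the main arms.** With 120:120 fixed by blocking and no stratification, the number k of a phenotype's m women who fall in one arm is approximately hypergeometric (240, m, 120). A binomial tail would overstate the risk. Expected efficiency relative to an exact 1:1 split is the mean of 4k(m−k)/m², which equals 1 − (240−m)/(239m). For m = 24 this is 1 − 216/5736 = 0.962. Power is for 70% against 50% within the phenotype, with a perfectly balanced split.

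| Women in phenotype (share) | P(2:1 or worse) | Expected efficiency | Power if balanced |
|---|---|---|---|
| 12 (5%) | 37.5% | 0.92 | 10% |
| 24 (10%) | 13.1% | 0.96 | 16% |
| 36 (15%) | 4.6% | 0.98 | 23% |
| 48 (20%) | 1.5% | 0.98 | 29% |
| 60 (25%) | 0.4% | 0.99 | 35% |

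The average loss within a phenotype is therefore about 1-8%. Even an actual 2:1 split is tolerable. With 36 women, the variance ratio is (1/24 + 1/12)/(1/18 + 1/18) = 1.125.

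**3. Imbalance in the primary comparison.** The difference in a phenotype's share between arms is (2k − m)/120. It reaches 10 points when |2k − m| ≥ 12. The hypergeometric probability is 10.1% for m = 60 (25% share) and 12.1% for m = 72 (30% share).

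If that phenotype's ovulation probability were 40 points higher, a 10-point imbalance would move the arm difference by 0.10 × 40 = 4 points, against a planned difference of 20. The planned standard error with 91 per group is √(0.21/91 + 0.25/91) = 7.1 points, so this shift is about 0.56 of a standard error.

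**4. What adjustment could remove.** For one phenotype with share p and ovulation difference δ against the rest, the share of outcome variance explained is about p(1−p)δ² / [0.60×0.40], where 0.60 is the mean of 70% and 50%.

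- p = 10%, δ = 20 points: 0.0036/0.24 = 1.5%
- p = 30%, δ = 40 points: 0.0336/0.24 = 14%

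**The case against.** The strongest reply is that the article contradicts nothing here. It names no stratification factor, but it never says that allocation is unstratified, and a condensed article may leave such details to the full protocol. That stands: a reader might infer that the trial is definitely unstratified, and the document does not support that much. Still, the allocation paragraph covers ratio, blocking, software and concealment, so a stratification factor would naturally have been named there.

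A second reply is that the phenotype analysis is exploratory, the trial is sized on GLC against letrozole, and blocked allocation without strata is an accepted design. This also stands. Low power within phenotypes comes from small numbers, which stratification does not change.

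A third reply concerns bias. A reader might infer that chance imbalance in phenotype biases the primary comparison. It does not: the imbalance is sampling variation already covered by the error rate of the test. The 4-point shift combines an unfavourable tail event with a 40-point difference that the article does not give.

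Finally, stratifying has a cost. The blinding described covers block sizes and myo-inositol or placebo, and GLC against letrozole is evidently open. Small blocks within several strata at one centre make the next assignment easier to guess. This argues for concealed, varying block sizes and few strata. It does not argue against covariate adjustment, which needs no change to allocation.

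**Conclusion.** The point holds as a minor design improvement. As described, neither the allocation nor the primary comparison uses phenotype, although phenotype has its own objective and is treated as a potential predictor of the primary outcome. The validity of the GLC-versus-letrozole test is not in question.

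The risk of a poor split is real only for phenotypes of about 10% of the sample or less. If the four phenotypes were equally common, it would be negligible for each. For the primary comparison, adjustment would remove roughly 1.5-14% of outcome variance. All these sizes rest on assumed phenotype shares, and the last also rests on assumed ovulation differences of 20-40 points.

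**What to change.** 1. **Adjust the primary comparison.** Specify GLC against letrozole with phenotype as a covariate, for example by logistic regression or a phenotype-stratified Mantel-Haenszel test in place of the unadjusted chi-square. This costs almost nothing, because phenotype follows from the entry diagnosis.
2. **State whether allocation is stratified.** If the full protocol already stratifies by phenotype, one sentence settles this part.
3. **If it does not, stratify the first-stage REDCap lists by phenotype before the first enrolment.** Merge rare strata and use concealed, randomly varying block sizes. The total of 240 is unchanged. The costs are new lists, a few incomplete blocks, recording phenotype before allocation, and slightly more predictable assignments.
4. **Keep the phenotype comparison labelled exploratory**, since neither change cures its low power.

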**Fig. 1 Fig1:**
[figure not shown]
Participants will be randomized into two groups: the “Graceful Lifestyle Changes” (GLC) group and the oral medication group. Both groups will be further randomized to receive either myo-inositol or its placebo

**Fig. 2 Fig2:**
[figure not shown]
Schedule of enrolment, interventions, and assessments

### Lifestyle intervention group (GLC)

The GLC group will have weekly check-ins with physicians and educators for 12 consecutive weeks. A wellness booklet designed and provided by clinicians will outline the main concepts being taught. Each week, subjects will receive detailed comprehensive instructions on how to follow a low-glycemic meal plan, incorporate walking 10,000 steps a day, and induce the relaxation response using cognitive behavioural therapy techniques. The low-glycemic-meal plan requires participants to consume 45% of carbohydrates in their diet and no more than 55 g of glycemic load a day, which is similar to previous low-glycemic diet intervention studies. Lists will be provided outlining foods that are low, medium, or high in their glycemic load. Hence, within their overall meal plan, participants will be advised to eat predominantly low-glycemic foods and to limit high-glycemic foods. They will also be provided with a pedometer to record the number of steps taken each day. These steps can be achieved by any form of exercise that participants can sustain. Lastly, participants will practice relaxation response exercises for 20 min daily on their own, in combination with 6 weeks of mindfulness training provided within the 12-week intervention program.

### Data collection

Participants will complete a 3-day food diary report during the baseline, 4th, 8th, and 12th weeks. Participants will also receive a phone call from a trained researcher to complete a 24-h diet recall at the end of the 2nd, 6th, and 10th weeks. This recall will assess all food consumed in the previous 24 h. These combined methods will aim to assess overall compliance to the low-glycemic diet, provide researchers with information on the length of time that participants take to comply, evaluate any fluctuations in eating habits and compare these two types of nutritional assessments.

Participants will also record their physical activity during the baseline, 4th, 8th, and 12th weeks based on their pedometer recordings and will record the meditation and relaxation exercises performed daily.

Compliance to the physical activity portion will be measured through daily pedometer readings recorded by the participant. Compliance will be ensured additionally through weekly check-ins/weigh-ins and frequent motivational email reminders.

Psychological well-being (depression, anxiety, stress, and quality of life) will be assessed before and after the 12-week intervention by two validated self-report questionnaires: the Depression Anxiety Stress Scale (DASS) and the Fertility-Related Quality of Life tool (FertiQoL) [27, 28].

### Letrozole group

The use of clomiphene citrate has been commonly used to treat anovulatory infertility. However, clinical experience and recent study evidence has suggested that letrozole is more effective than clomiphene citrate in achieving ovulation in PCOS [29]. Additionally, letrozole does not negatively affect endometrial thickness. The initial dose will be 5 mg daily for 5 days which can be increased to a total daily dose of 7.5 mg, if necessary, depending on the ovulatory response as per current clinical practice at the Grace Fertility Centre. The first dose will be defined as “cycle day 3” which corresponds to cycle day 3 of spontaneous menses or day 3 of an induced withdrawal bleed following progestogen withdrawal. This treatment regimen will continue for three cycles or until pregnancy is achieved. Subjects will be advised to have intercourse every other day during the expected ovulatory period (beginning cycle day 12, for a week) and to use urinary ovulation prediction kits.

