**Methods/design:**

This is a randomized controlled trial which will include 240 women diagnosed with PCOS, according to the Rotterdam criteria, who are trying to conceive. Participants will be randomized to either a comprehensive lifestyle intervention program or prescribed an oral fertility medication, letrozole. These two groups will be further randomized to consume either myo-inositol or a placebo. Participants will be between the ages of 18 and 37 years. Exclusion criteria include women who have already begun fertility treatment, who are currently using myo-inositol or have taken it within the past 3 months, or who are being treated for, or have a history of, an eating disorder. The primary outcome will be the ovulation rate, the secondary outcome will be conception. Other outcomes include miscarriage rates, validated rating measures of overall quality of life (including social, relational, mind/body and emotional sub-categories) and mental health scores (depression, anxiety, and stress).

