## Background

Polycystic ovary syndrome (PCOS) is a heterogenous endocrine syndrome characterized by chronic anovulation and hyperandrogenism (clinical or biochemical) according to the original 1990 NIH criteria. The 2003 Rotterdam criteria added the presence of polycystic ovarian morphology on ultrasound which resulted in four distinct PCOS phenotypes. PCOS is also associated with obesity, insulin resistance, metabolic syndrome, reduced quality of life, increased anxiety and higher rates of depression [1]. Between 70 and 80% of women with PCOS have difficulty conceiving due to oligo- or anovulation. Despite ovulation rates of 75–80% achieved with the use of ovulation-induction agents and a conception rate per cycle of 22% (comparable to that of a healthy women trying to conceive naturally in their first year), some women with PCOS remain unresponsive [2, 3]. In contrast, evidence suggests that lifestyle (diet, activity and stress management) influences ovulation and the effectiveness of fertility treatments [4–6].

While lifestyle intervention is recommended as first-line management for women with PCOS and obesity, 45% of women with PCOS reported that they have never received information on lifestyle management and only 61–76% of reproductive endocrinology and infertility obstetric gynecologists (REI-ObGyn) and 46–61% of obstetric gynecologists (ObGyn) recommended lifestyle modifications to patients for fertility or non-fertility problems [7, 8]. Even with efforts to improve dietary and exercise habits, women with PCOS often have difficulty managing their weight. In addition, 62% of women with PCOS reported never receiving information about emotional support or counseling [7]. It appears that attention to general physical and psychological health is inconsistent at the clinical level yet recognized as an important factor in the effective management of women receiving the life-altering diagnosis of PCOS and/or infertility [9, 10].

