### Outcomes

Ovulation is the primary outcome (categorical “yes” or “no”) and frequency of ovulation (nominal “0”, “1”, “2”, or “3”) during the 12-week (84-day) study. The study length allows observation of three potential ovulatory cycles. The upper limit of a normal ovulatory cycle length is 35 days, hence, to document ovulation using progesterone levels in the expected luteal phase, the study may extend to the end of week 14. Ovulation will be identified by assessing the serum progesterone level on day 22 and, if appropriate, will be repeated 1 week later. A progesterone level greater than 10 nmol/L will be used to confirm ovulation. The secondary outcome is conception (categorical “yes” or “no”). Other outcomes that will be evaluated are miscarriage rates, changes in numerical scores of depression, anxiety, stress, and quality of life based on the DASS and the FertiQoL.

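### As written, advice on intercourse frequency and ovulation kits goes only to the letrozole arm, which could contribute to a GLC-versus-letrozole difference in conception (minor)

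*Protocol article*

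**What the plan says.** - **Population.** The abstract (Methods/design) reads "This is a randomized controlled trial which will include 240 women diagnosed with PCOS, according to the Rotterdam criteria, who are trying to conceive". The wish to conceive is common to both arms.
- **Letrozole arm.** Overall study design states that "the second group will be prescribed letrozole to induce ovulation, with the standard physician counseling". The Letrozole group section ties the first dose to cycle day 3, "which corresponds to cycle day 3 of spontaneous menses or day 3 of an induced withdrawal bleed following progestogen withdrawal". It then says "Subjects will be advised to have intercourse every other day during the expected ovulatory period (beginning cycle day 12, for a week", and in the same sentence recommends urinary ovulation prediction kits.
- **GLC arm.** The Lifestyle intervention group section says that "subjects will receive detailed comprehensive instructions on how to follow a low-glycemic meal plan, incorporate walking 10,000 steps a day", followed by relaxation exercises and mindfulness training. It also provides a booklet, food lists and a pedometer, and states "The GLC group will have weekly check-ins with physicians and educators for 12 consecutive weeks". Neither intercourse nor ovulation kits are mentioned.
- **Outcomes.** The primary outcome is ovulation, confirmed by serum progesterone above 10 nmol/L. "The secondary outcome is conception", recorded as yes or no.
- **Emphasis.** Potential biases or limitations describes pregnancy as the main goal of the intervention, so readers are likely to give the conception result weight.

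**The concern.** The frequency and timing of intercourse can change the chance of conception in a woman who ovulates, whichever arm she is in. If only one arm is advised on this, the arms could differ in conception even if GLC and letrozole restored ovulation equally well. Randomisation does not protect against a difference introduced after allocation. Because the advice is given by arm, no later analysis can separate its effect from that of the treatment.

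What is at stake is how one secondary outcome is read: whether a conception difference reflects letrozole versus lifestyle, or partly the conception advice that accompanies letrozole.

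**Working it through.** **Which arm gets the advice.** The advice appears once, under Letrozole group, directly after the dosing and cycle rules. The GLC section uses the same word for its participants (subjects) when it means only its own arm, so the natural reading is that each section speaks of its own arm. Overall study design, Data collection, Myo-inositol group and Outcomes do not extend the advice to both arms. Overall study design attaches standard physician counselling to letrozole only.

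**Which outcomes can be affected.** Ovulation is a progesterone measurement and does not depend directly on intercourse or kits. Conception does. Myo-inositol or placebo is randomised within each arm, so the advice is balanced across that comparison.

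**The plan's own figure.** No sample size is stated for conception. The stated 91 per group rests on ovulation (70% versus 50%, 5% level, 80% power) and reproduces with the two-sided unpooled normal formula:

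n = (1.960 + 0.842)² × (0.70×0.30 + 0.50×0.50) / 0.20² = 7.849 × 0.46 / 0.04 = 90.3, so 91 per group and 182 in total.

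The advice does not enter this calculation.

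**Illustration of size.** Inputs:

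- 22% conception per cycle, from Background: "a conception rate per cycle of 22% (comparable to that of a healthy women trying to conceive naturally in their first year". It is applied here to ovulatory cycles with the advice.
- 22% (no effect) down to 15% without the advice. The 15% is an assumption with no source in the documents.
- Three cycles (Outcomes).
- Ovulation of 50% or 70%, the median row of Table 1, set equal in both arms so that any gap is due to the advice alone.
- 91 or 120 women per arm (Sample size and power calculations).

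Table 1's rates are used as proportions of women, and the primary outcome is yes or no over 12 weeks. So let s be the share of women who ovulate at least once, and c the conception rate per ovulatory cycle. Two extreme patterns are:

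- *Independent cycles:* per-cycle ovulation k = 1 − (1 − s)^(1/3), which is 20.6% at s = 50% and 33.1% at s = 70%. Conception = 1 − (1 − k·c)³.
- *All three cycles or none:* conception = s × [1 − (1 − c)³].

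The 95% half-width is 1.96 × √[p1(1 − p1)/n + p2(1 − p2)/n]. At the worst case, c = 22% versus 15%:

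| s | Pattern | With advice | Without | Gap (points) | Half-width, n = 91 / 120 |
|---|---|---|---|---|---|
| 50% | Independent | 13.0% | 9.0% | 4.0 | 9.1 / 7.9 |
| 50% | All or none | 26.3% | 19.3% | 7.0 | 12.2 / 10.6 |
| 70% | Independent | 20.3% | 14.2% | 6.1 | 10.9 / 9.5 |
| 70% | All or none | 36.8% | 27.0% | 9.8 | 13.5 / 11.7 |

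With c = 22% in both arms the gap is zero. In every row it is below the half-width.

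**Sensitivity to the reading of the rates.** If 50% and 70% were per-cycle rates, conception = 1 − (1 − s·c)³. The worst-case gaps are then 29.5% − 20.9% = 8.6 points and 39.5% − 28.3% = 11.1 points (from unrounded values), still below the smallest half-widths of 10.9 and 11.9. If 22% applied to every treatment cycle regardless of ovulation, the gap would be 52.5% − 38.6% = 14.0 points, against half-widths of 14.3 (n = 91) and 12.5 (n = 120). Only this last case, at 120 per arm, exceeds the sampling error.

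**The case against.** The strongest reply is that this is a comparison of disclosed packages. The article pairs letrozole with standard physician counselling, GLC is itself a bundle, and the objectives in Background concern ovulation, insulin resistance, metabolic parameters and phenotypes, not conception. Nothing attributes a conception difference to the drug alone. This stands: conception remains a valid comparison of the two packages as delivered. It does not answer why women in one arm, equally trying to conceive, should go without simple conception advice.

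Second, the article condenses a fuller protocol. The GLC booklet and the weekly check-ins with physicians may already contain the advice, and no sentence says GLC women are denied it. The article is also loose about arms elsewhere: Data collection speaks of participants in general while describing largely GLC-specific measures. This stands as a limit on certainty. The point is about what the article states, and if GLC women do receive the advice, one sentence settles it.

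Third, the day-12 window follows from letrozole dosing and does not carry over to irregular GLC cycles. Agreed. What can be shared is advice on regular intercourse and on kits.

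A reader might go further and infer that the conception comparison is biased against GLC. The documents do not support that. GLC women also receive weekly contact, group support and frequent emails that are not described for the letrozole arm, so the net direction is open. No effect of the advice is given, and Background calls the 22% rate comparable to natural conception, so the effect may be zero.

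**Conclusion.** The point holds as a minor one. The article states a conception-relevant co-intervention for one randomised arm only, and it could contribute to a GLC-versus-letrozole difference in conception. Taken alone it would favour letrozole; the net direction and the size cannot be derived from the documents.

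With Table 1's rates read as the share of women ovulating, the illustrative gap runs from 0 to at most about 4 to 7 points at 50% ovulation and 6 to 10 points at 70%, below the sampling error. This rests on equal ovulation in both arms, three cycles, 22% per ovulatory cycle with the advice, and the unsourced 15% without it.

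It would be wrong to infer that the main result is compromised. Progesterone-confirmed ovulation, the sample size of 91 (enrolling 120) per group and the randomised myo-inositol comparison are unaffected, and no stated figure is in error.

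**What to change.** Before recruitment, give GLC women equivalent conception advice at the existing weekly check-ins and in the booklet:

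- regular intercourse, such as every other day around the expected or kit-indicated ovulatory period;
- ovulation kits on the same terms of advice and supply as in the letrozole arm, without relying on kits alone in irregular cycles, because the documents do not show how well kits work there.

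Keep the day-12 window for letrozole cycles. If GLC women already receive such advice, say so in the GLC section. If the difference is intended, state that the conception result compares two care packages as delivered and is not attributable to letrozole versus lifestyle alone.

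The cost is a wording change and, if kits are supplied, a small kit cost. No extra visits are needed, and Trial status says recruitment has not begun. The downsides are that GLC becomes slightly less purely a lifestyle program, and that the advice would be equivalent but not identical in the two arms.
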